### Definition of intervention, control and standard care

#### Intervention

Participants in the intervention group will receive injections of 0.1–0.3 millilitres of sterile water for injection into four anatomical points surrounding the Michaelis rhomboid over the sacral area, two over the posterior superior iliac spines (PSIS) and the remaining two at two centimetres posterior, and one centimetre medial, to the PSIS respectively (Figure 
3). This is a standard approach described in the majority of previous trials and has been demonstrated to be the most effective technique
[34,48]. The actual volume injected, which may vary slightly depending on minor differences in tissue depth, is determined by a visual assessment of the resulting ‘bleb’ or blister. Minor discrepancies or changes to the anatomical position, depth or alignment of the four injections have not been shown to impact on any analgesic effect
[51]. Injections will be given using 23 gauge needles or similar depending on actual equipment available at each site. One repeat injection will be provided for women who request them. Education sessions will be provided at all sites by the project manager, who has developed a dedicated ‘train the trainer’ course. All clinicians administering SWI will to be credentialed in this technique.

**Figure 3 F3:**
[figure not shown]
Injection sites for administration – control and intervention.

#### Control

Participants in the control group will receive 0.1 – 0.3 millilitres of normal saline 0.9% for injection into the same four anatomical points surrounding the Michaelis rhomboid as previously described. Repeat injections will also be provided as required (Figure 
3).

#### Care during labour

All women will receive care throughout labour and birth as required according to routine Australian clinical practice; including access to the usual analgesic options. Preliminary planning using data from perinatal databases at each site reveals that non-pharmacological and pharmacological analgesic options are similar; and have been incorporated into our definition of ‘standard care’. Non-pharmacological options include water immersion, aromatherapy, massage, and hot showers. Pharmacological options include Nitrous Oxide inhalation, narcotics (pethidine and morphine) and epidural or spinal anaesthesia. Intervention rates (e.g., epidural and CS) are similar across sites. At a number of current and planned research sites SWI is not available as standard care (demonstrating the importance of research in this area). Sterile water injections are available at site one, two and four, and women requesting SWI at these sites will not be entered into the trial.

### Randomisation and blinding

Blinded (plain label) ampoules of sterile water (intervention) and normal saline (placebo) for injection will be prepared by the Mater Health Service Pharmacy for all sites, and labelled according to a randomisation schedule prepared by the Mater Medical Research Institute. The ampoules will be delivered to each of the sites and stored in a locked container. The randomisation schedule will use permuted blocks and will be stratified by research site. In our previous trial about 10% of participants requested a repeat dose, to provide for this with minimal crossover between groups (e.g., women randomised to normal saline receiving sterile water as a repeat dose) each allocation packet will include two ampoules of the allocated treatment. Following consent, two midwives (other than the midwife assigned to provide the woman’s care in labour, or ‘primary midwife’) will obtain the next ampoule in numbered order and administer the injections. As this is a double blind trial, the administering midwives will be unaware of the arm to which the participant has been allocated. The ampoule number will be recorded in a research log and on the data collection forms. As the injection of normal saline does not result in the same degree of administration pain as sterile water, both interventions will be administered by midwives other than the primary midwife, who will be absent from the room throughout. This will prevent the primary midwife from observing the woman’s reaction to the administration which reduces the likelihood of assumptions being made about the arm of the trial into which the woman has been randomised.

## Outcome measures

### Primary outcome

•Proportion of women who have a CS in labour

### Secondary outcomes

•Proportion of women undergoing induction and/or augmentation of labour

•Proportion of women receiving epidural anaesthesia

•Proportion of women having instrumental vaginal births

•Primary indication for CS

•Visual analogue scale of back pain prior to SWI

•Visual analogue scale of back pain following SWI (10, 45 minutes)

•Length of 1st stage and 2nd stage of labour

•Results of most recent vaginal assessment prior to randomisation

•Position of fetal occiput in relation to the maternal pelvis prior to randomisation and how this was determined

•Proportion of women breastfeeding at discharge

•Proportion of neonates admitted to the neonatal intensive care unit

•Cost of care from admission in labour until discharge of mother and baby from hospital from the perspective of the health system.

•Experience of satisfaction, relaxation, social support, negative side effects and memory of pain.

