#### Inclusion criteria

Women who:

•In labour (spontaneous or induced, but not dependent on degree of cervical dilation)

•Are ≥ (equal to or greater than) 18 years of age

•Have a term singleton pregnancy (between 37 + 0 and 41 + 6 weeks gestation)

•Have a fetus in a cephalic (head down) presentation

•Experience back pain assessed by visual analogue scale VAS as ≥ 7 when women request analgesia for back pain

•Are able to provide informed consent.

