When women are in labour, they typically present to the Birth Suite of their respective hospital. Women will not be asked to consent to participation until such time as they have been fully assessed for eligibility against the inclusion and exclusion criteria. Although the majority of women will have received information regarding the trial during pregnancy, on admission to Birth Suite, staff will remind them of the trial and offer interested, and potentially eligible, women another copy of the PICF, and answer any outstanding questions.

Consent processes will be undertaken by the clinical trial co-ordinator at each site, or in their absence, a midwife who is not providing direct care to the woman. In our previous trial
[48], women had no objections to consenting in labour, and when they were requesting analgesia for back pain. However as consent for clinical care differs from that required for research, if the person seeking consent considers that labour is too far advanced, or for any other reason staff consider women to be incapable of considering all available choices in clinical care, and of making an informed and voluntary consent, participation in the trial will not be sought.

Once the consent process has been completed, the woman will be randomised.

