## Data analysis

### Statistical methods

All women who underwent randomisation will be analysed in their allocated treatment groups (ie. intention to treat). Relative risks with 95% confidence intervals for the primary outcome will be calculated. Secondary outcome measures of categorical data will be analysed with chi-squared tests and continuous data will be analysed with t-tests for normally distributed data and Mann–Whitney *U* test for parametric data. Regression will be used if necessary to adjust for any other confounding variables. All study outcomes will be analysed using a two-sided P value of < 0.05 to indicate statistical significance. The study is only powered to report the primary outcome and for secondary outcomes confidence intervals (CI) will be included as a measure of the effect size. Differences in pre and post VAS scores will be reported in the format recommended by the recent Cochrane Review
[54].

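### Secondary outcomes include variables settled before treatment and pool induction with augmentation, so some tests can show only chance and any augmentation risk ratio is pulled toward 1

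*Protocol article*

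**What the plan says.** Under Secondary outcomes, the protocol article lists as a single proportion: "Proportion of women undergoing induction and/or augmentation of labour".

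The same list includes three items that their own labels place before treatment:

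- on pain, the entry reads "Visual analogue scale of back pain prior to SWI"
- on the examination in labour, it reads "Results of most recent vaginal assessment prior to randomisation"
- on how the baby is lying, it reads "Position of fetal occiput in relation to the maternal pelvis prior to randomisation and how this was determined"

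The Inclusion criteria admit women who are "In labour (spontaneous or induced, but not dependent on degree of cervical dilation" and who "Experience back pain assessed by visual analogue scale VAS as ≥ 7 when women request analgesia for back pain". Under Recruitment and consent process, eligibility is assessed first, and then: "Once the consent process has been completed, the woman will be randomised".

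The Statistical methods section says: "Secondary outcome measures of categorical data will be analysed with chi-squared tests". Continuous outcomes get a t-test or a Mann–Whitney test. A two-sided P below 0.05 marks significance for all study outcomes. The section adds that the trial is powered only for the primary outcome, that confidence intervals will be given for secondary outcomes as a measure of effect size, and that pre/post differences in pain score will be reported.

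**The concern.** An outcome should be something the injections could change. Three listed items cannot be changed, because they are recorded before the injection or before randomisation. In a properly randomised trial the null hypothesis is true for each of them, so a between-group test can yield only a correct non-rejection or a false positive.

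Induction has the same problem in a less visible form. Whether labour was spontaneous or induced is known when a woman is assessed for entry. Every induced woman therefore counts as an event in the pooled outcome whichever arm she is in. If the injections change the need for augmentation, the pooled risk ratio understates that change, and so does the confidence interval promised as a measure of effect size. If they do not, the pooled result is merely uninformative; it is not biased away from the null.

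**Working it through.** **Inputs.** From the protocol article: 839 women per group (Sample size) and two-sided alpha of 0.05 (Statistical methods). It gives no induction rate, augmentation rate or expected effect on augmentation. The following are assumptions: induced share I of 20%, 30% or 40%, equal in both arms; augmentation among the remaining women of 40% in control and 32% with sterile water (risk ratio 0.80).

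**The plan's own figure.** For 17.5% v 12.5% at 80% power, the standard two-proportion formula gives 800 per group, and 839 with the continuity correction. The stated 839 is reproduced and is not in dispute. It is used here as the number analysed.

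**Tests on pre-treatment items.** The chance of at least one false positive among k independent items, one test each, is 1 − 0.95^k.

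- Two items (vaginal assessment, fetal position): 1 − 0.95² = 9.8%.
- Three items (adding pre-injection pain): 1 − 0.95³ = 14.3%.

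**Dilution.** With a the control augmentation proportion among non-induced women and RR its true ratio, the pooled proportions are c0 = I + (1 − I)·a and c1 = I + (1 − I)·a·RR. When I is above 0 and RR is below 1, c1/c0 lies strictly between RR and 1. The direction therefore needs no assumed rate.

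At I = 30%: c0 = 0.30 + 0.70 × 0.40 = 0.580, c1 = 0.30 + 0.70 × 0.32 = 0.524, and the ratio is 0.524/0.580 = 0.903.

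**Power.** With d = p0 − p1 and p̄ the mean of p0 and p1:

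power = Φ{[d√n − 1.96·√(2p̄(1 − p̄))] / √(p0(1 − p0) + p1(1 − p1))}

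At I = 30%:

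- Pooled outcome, n = 839: (0.056 × 28.97 − 1.96 × 0.7033)/0.7022 = 0.347, power 64%.
- Augmentation among women in spontaneous labour, n = 0.70 × 839 = 587: (0.08 × 24.23 − 1.96 × 0.6788)/0.6765 = 0.899, power 82%.
- Augmentation in all 839, induced women as non-events, 28.0% v 22.4%: (0.056 × 28.97 − 1.96 × 0.6140)/0.6127 = 0.683, power 75%.

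| Induced | Pooled outcome | Pooled RR | Power, pooled | Power, spontaneous labour only | Power, all women |
|---|---|---|---|---|---|
| 20% | 52.0% v 45.6% | 0.88 | 75% | 86% | 83% |
| 30% | 58.0% v 52.4% | 0.90 | 64% | 82% | 75% |
| 40% | 64.0% v 59.2% | 0.93 | 52% | 75% | 67% |

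**Sensitivity.** Adding control augmentation of 30% (ratios 0.7 and 0.8) and 20% (ratio 0.7), the pooled ratio runs from 0.84 to 0.94. Power is 31–85% pooled, against 57–97% in spontaneous labour.

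**Which gains are general.** The squared signal-to-noise ratio of the spontaneous-labour analysis exceeds that of the pooled outcome by about c/a (arm averages; at I = 30%, 0.552/0.36 = 1.53). Since c is always larger than a, this gain holds at any rates. The all-women version has the same absolute difference as the pooled outcome and gains only through a smaller variance. That requires (1 − I)a to lie further from one half than c, which reduces to a below 50%.

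**The case against.** The strongest reply is that little hangs on this. The protocol disclaims power for anything but the primary outcome, so lost power on a secondary outcome is a weak harm. That stands, and it limits the weight of the point. It does not answer the attenuation, because the promised confidence interval would be centred on a diluted ratio at any sample size.

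Second, the labels themselves say that these items precede treatment, and recording how fetal position was determined is plainly a data item. A reader might infer that the trial will present chance imbalances as treatment effects. The documents do not say so. What they do is place the items under outcomes and apply the significance threshold to all outcomes without exception.

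Third, pre-injection pain has a legitimate role as half of the pre/post comparison. That is correct; the fault lies in listing it as a separate outcome, not in measuring it. This is why the two-item figure of about 10% is given beside 14%. Both figures assume independence and one test per item, which the documents do not establish.

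Fourth, the and/or wording may allow induction and augmentation to be reported separately. Possibly, but the text names one proportion.

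A reader might also infer that a real effect on augmentation is being hidden. The protocol claims no such effect. Nor does the missing time anchor for epidural support a criticism, since a condensed article may leave that detail to the full protocol.

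**Conclusion.** The point holds as a matter of classification. Three listed outcomes are baseline measurements and induction is settled at entry, yet the plan as written tests them as outcomes. Attenuation of any augmentation risk ratio follows from the definition alone. Its size does not: 0.80 becoming 0.88–0.93, and power of 75–52% against 86–75% (spontaneous labour) or 83–67% (all women), rest on assumed rates and matter only if the injections change augmentation. The 10% and 14% figures rest on independence and single tests.

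A reader might take this as a threat to the trial's main conclusion. It is not: caesarean section in labour, its analysis and the sample size are unaffected. This is a minor improvement.

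**What to change.** 1. Move onset of labour (spontaneous or induced), last vaginal assessment, fetal position and pre-injection pain score to a baseline table, described by arm without significance tests. Keep pre-injection pain for the pre/post pain comparison.
2. Replace the pooled proportion with augmentation alone. Analyse it among women whose labour began spontaneously, or in all women with onset of labour as a covariate. Either is valid because onset precedes randomisation.
3. Count augmentation begun after randomisation where a start time is available.

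The cost is an edit to the outcome list and possibly one extra field. Under Data sources, obstetric outcomes come from hospital or state perinatal databases, and nothing there says that these hold augmentation start times, so a time may have to be recorded on the trial form. A spontaneous-labour analysis uses fewer women (587 instead of 839 per group at 30% induced), although in the calculation above it still has more power than the pooled outcome.

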### Lower back pain in labour – a significant problem

One in three women will experience continuous lower back pain in labour
[17]. The occipito-posterior (OP) position of the fetus has been cited as a common contributing factor
[18] although there is a paucity of evidence to support or refute this observation
[19]. The OP position results in deflexion of the fetal head, which then presents a larger diameter as it enters and progresses through the maternal pelvis, hence contributing to obstructed labour and an increased risk of interventions including epidural anaesthesia and caesarean section
[20]. Labour dystocia, characterised by very slow progress in labour together with significant and prolonged pain, further increases the risk of intervention, particularly epidural anaesthetic and CS
[20]. Indeed, labour dystocia has been reported as the major reason for a CS during labour
[21]. However, due to differences in Australian state and territory perinatal reporting, no data are available on the actual number performed for this reason. That said, a major Australian metropolitan hospital reported labour dystocia as the primary indication for 12.4% of all CSs performed in 2007
[22], with other research suggesting it was more common in women having their first baby (primiparous), accounting for nearly 80% of CSs performed during labour
[23].

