### Sample size

The meta-analysis of SWI use reported the overall rate of ‘in labour’ CS as 9.9% in the control group and 4.6% in the intervention (SWI) group
[36] – i.e. a greater than 50% reduction in the CS rate in the SWI group. However, the review included trials where women receiving SWI were compared with women receiving either a placebo or other interventions (eg. acupuncture), and included trials that were conducted over two decades ago (1990 to 2008): a significant increase in CS rates (% in 1991
[49] to 31.5% in 2009
[50]) has been recorded in the intervening period.

More recently, at a metropolitan hospital in QLD, routine birth outcome data were collected on all women in labour who received SWI during 2010 (n = 427). The CS rate for women in the SWI group was 12.5%. The ‘in labour’ CS rate for women receiving standard care during the same period was 17.5%. This represents a difference of 30% which we suggest may conservatively reflect the contemporary clinical trend in CS rates. To demonstrate a similar reduction (17.5% to 12.5%), our study requires 839 women in each group (80% power, type I error 0.05). The attrition rate in our previous trial was 13%
[48], however this was largely due to women giving birth prior to the measurement of the primary outcome (pain at 30 mins) and the use of nitrous oxide inhalation prior to randomisation. Neither of these are exclusion factors in this trial, therefore we expect attrition to be minimal and propose an attrition rate of 10%. The total sample size required is therefore 1886 women. As some sites have higher annual birth rates than other sites, the recruitment allocation anticipated for each site will be proportional.

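### The indication for caesarean is a secondary outcome with no stated denominator; a literal test would compare arms only among women who had the primary event

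*Protocol article*

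**What the plan says.** The primary outcome (Primary outcome) is "Proportion of women who have a CS in labour". The list under Secondary outcomes includes "Primary indication for CS", with no denominator, categories or effect measure.

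Statistical methods gives four general rules that bear on it:

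- Population: "All women who underwent randomisation will be analysed in their allocated treatment groups (ie. intention to treat").
- Test: "Secondary outcome measures of categorical data will be analysed with chi-squared tests".
- Significance: "All study outcomes will be analysed using a two-sided P value of < 0.05 to indicate statistical significance".
- Status: "The study is only powered to report the primary outcome and for secondary outcomes confidence intervals (CI) will be included" as a measure of effect size.

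Sample size plans for CS rates of 17.5% under control and 12.5% under sterile water, with 839 women per group. The background section on lower back pain says that "labour dystocia has been reported as the major reason for a CS during labour". It also cites a share of nearly 80% of in-labour caesareans in women having a first baby.

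**The concern.** An indication exists only where a caesarean was done. Applying the general chi-squared rule to this variable as it stands therefore drops every woman without a CS and compares arms within a group selected by the primary outcome. If sterile water changes the CS rate, the women with a CS in the two arms are differently selected groups, and the contrast between them is not a randomised one. It also sits poorly with the rule that all randomised women are analysed.

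Shares within that group must sum to 100%, so a fall in one indication raises the shares of the others even when their risk is unchanged. Conversely, if all indications fell in the same proportion, the shares would be identical and the test would show nothing. At stake is whether this outcome can say which caesareans the intervention prevents.

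**Working it through.** **Inputs.** From Sample size: CS rates of 17.5% (control) and 12.5% (sterile water), 839 per group, 80% power, alpha 0.05. From the background: a dystocia share of nearly 80% of in-labour CS in first-time mothers. The article gives no share for the trial population, so a range of 40% to 80% is assumed.

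**Step 1: reproduce the plan's figure.** The pooled-variance formula for two proportions, two-sided, gives

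n0 = [1.960 × √(2 × 0.15 × 0.85) + 0.8416 × √(0.175 × 0.825 + 0.125 × 0.875)]² / 0.05² = 799.4, i.e. 800.

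With the continuity correction,

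n = (n0/4) × [1 + √(1 + 4/(n0 × 0.05))]² = 839.

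This matches the plan, so its rates and group size can be used as they stand.

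**Step 2: expected caesareans.** 839 × 0.175 = 146.8 and 839 × 0.125 = 104.9, so about 147 and 105.

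**Step 3: scenario.** Assume that sterile water removes only dystocia caesareans. Let s be the dystocia share of control CS.

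- CS for other indications, per randomised woman: 17.5% × (1 − s) in both arms, so the relative risk (RR) is 1.00.
- Share of other indications among women with a CS: (1 − s) under control and (1 − s) × 17.5/12.5 = 1.40 × (1 − s) under sterile water.
- CS for dystocia, per randomised woman: 17.5% × s under control and 17.5% × s − 5% under sterile water.

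The scenario is possible only if s is at least 5/17.5 = 28.6%.

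**Step 4: results** at 839 per arm, with indications grouped as dystocia or other (the article states no categories) and an uncorrected chi-squared test:

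| Assumed s | Other indications, share of CS: control v sterile water | p, women with CS only | Other indications, % of randomised, each arm | Dystocia CS, % of randomised: control v sterile water | RR, dystocia CS |
|---|---|---|---|---|---|
| 40% | 60% v 84% | < 0.001 | 10.5 | 7.0 v 2.0 | 0.29 |
| 50% | 50% v 70% | 0.0015 | 8.75 | 8.75 v 3.75 | 0.43 |
| 60% | 40% v 56% | 0.012 | 7.0 | 10.5 v 5.5 | 0.52 |
| 70% | 30% v 42% | 0.049 | 5.25 | 12.25 v 7.25 | 0.59 |
| 80% | 20% v 28% | 0.14 | 3.5 | 14.0 v 9.0 | 0.64 |

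The 1.40-fold rise is the same in every row. It is nominally significant up to a dystocia share of about 70%, while the risk per randomised woman does not differ at all.

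**Step 5: the same data with the other denominator.** At s = 80% the CS-only test gives p = 0.14. Per randomised woman, dystocia CS is 14.0% v 9.0%, RR 0.64, p = 0.001. The CS-only comparison can thus miss a real effect as well as suggest a shift that is not there.

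**Step 6: proportional effect.** If every indication fell by the same factor, 12.5/17.5 = 0.714, dystocia CS would fall by 29% and the shares among women with a CS would be identical in the two arms.

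**The case against.** The strongest reply is that the article fixes no such analysis. The item is a bare label, and the only population rule is intention to treat. That rule is compatible with the valid version: each indication per randomised woman, or no CS as its own category. Only 5 of the 13 listed items are worded as proportions. Several, such as pain before the injections and fetal position before randomisation, can only be descriptive. The denominator of one secondary outcome could also sit in an analysis plan or full protocol that is not shown.

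Much of this stands. A reader might infer that a CS-only test is explicitly planned; the article does not say so. But the intention-to-treat sentence fixes the arm in which a woman is counted and gives no indication value to a woman without a CS. Nothing marks this item as descriptive, and the chi-squared and significance rules are general. The literal result is therefore the weaker comparison.

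Two further inferences are tempting and not supported:

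- *That this is the one outcome testing the mechanism.* The aims give it no such role. Epidural use, augmentation, instrumental birth and length of labour are also listed and bear on the same pathway.
- *That it would create a false safety signal.* A reader would have to take shares as risks and ignore the fall in total CS, which is reported as the primary outcome. At the one in-labour share that the article cites, nearly 80%, the shift is not nominally significant.

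The scenario is also chosen. The background gives another figure, dystocia as primary indication for 12.4% of caesareans at one hospital, but its denominator is all caesareans and not those in labour. It cannot be used as s.

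**Conclusion.** The point holds as a weakness in how one secondary outcome is defined. It is an outcome without a denominator, paired with a general significance test, and the literal reading conditions on the primary outcome. At the plan's own CS rates, the resulting distortion is a 1.40-fold rise in the share of other indications with no change in their risk per randomised woman. This rests on the assumption that only dystocia caesareans are prevented. The p-values also depend on the assumed dystocia share and on the two-category grouping. The primary analysis and the sample size are untouched. The change is worth making because it replaces a comparison that randomisation does not protect with one that it does.

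**What to change.** In Secondary outcomes, replace the item with two: the proportion of all randomised women having a CS for dystocia, and the proportion of all randomised women having a CS for each other primary indication. Report each as a relative risk with 95% confidence interval. Give the breakdown of indications among women with a CS as description only, without a test. The cost is a line or two of outcome wording: the same data are used, no extra women are needed, and the result agrees with the intention-to-treat rule already in the article.

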### Review of previous trials of SWI in labour and effect on CS rates

A systematic review and meta-analysis
[36] undertaken on SWI reported significant limitations. The meta-analysis included eight trials involving 828 women and found a CS rate of 4.6% in the sterile water injection groups and 9.9% in the control groups (RR 0.51, 95% CI: 0.30-0.87)
[36]. Women in the control groups received normal saline placebo (six trials), acupuncture (one trial) and standard care defined as massage, water immersion and unrestricted mobilisation or transcutaneous electronic nerve stimulation (one trial). The authors reviewed the original publications of trial results and identified the following limitations:

•Only two reported a sample size calculation *a priori*[37,38]

•The method of allocation concealment was not described in two trials
[39,40]

•It was unclear if the outcome assessment was blinded in two trials
[39,41]

•Only one trial reported complete data on pain scores as many women gave birth prior to the final data collection point
[37]

•Two trials did not report if additional modes of pain relief had been used following the SWI intervention
[37,38]

•Only one of the investigators reported rates of cephalopelvic disproportion between groups
[41].

The trials were all relatively small, were heterogeneous using different techniques for administering SWIs and assessing outcome measures, and contained a number of potential biases. With these limitations, it is impossible to attribute any relationship between lower CS rates in the sterile water group to the administration of SWI. Further, none of these trials had investigated the relationship between SWI and CS as the primary outcome; to our knowledge, no such study has been undertaken. The authors of the meta-analysis, noting the reduction in CS rates and the limitations in the current literature, recommended a large trial with CS as the primary outcome. The National Institute of Clinical Excellence (NICE) guidelines
[33] also call for research into the effect of SWI on birth outcomes. With these issues in mind, we have designed the trial outlined in this protocol following the Consolidated Standards of Reporting Trials (CONSORT) guidelines
[42].

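### The 45-minute back-pain score does not exist for women who have already given birth, so the 45-minute comparison describes only women still in labour (minor, secondary outcome)

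*Protocol article*

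**What the plan says.** Secondary outcomes lists a baseline back-pain score and "Visual analogue scale of back pain following SWI (10, 45 minutes"). Relief of back pain is the first of the Secondary aims, and the Discussion says the trial will supply strong evidence on it.

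Four other places bear on whether the 45-minute score can be obtained:

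- The Background review of previous trials lists as a limitation: "Only one trial reported complete data on pain scores as many women gave birth prior to the final data collection point".
- Sample size: "The attrition rate in our previous trial was 13"%, and "this was largely due to women giving birth prior to the measurement of the primary outcome (pain at 30 mins"); a second cause, nitrous oxide before randomisation, is named beside it. Neither is an exclusion factor here, and the section concludes "therefore we expect attrition to be minimal and propose an attrition rate of 10"%.
- Inclusion criteria admits women in labour, "spontaneous or induced, but not dependent on degree of cervical dilation". The Recruitment and consent process section adds that participation is not sought when labour is judged too far advanced.
- Statistical methods: "All women who underwent randomisation will be analysed in their allocated treatment groups". Continuous secondary outcomes get a t-test or a Mann–Whitney test, regression is used if needed for confounding, and before-and-after VAS differences follow a format recommended by a Cochrane review. The study is powered for the primary outcome only.

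**The concern.** The attrition argument in Sample size is sound for caesarean section, because mode of birth is known for every woman who delivers. It does not carry over to a pain score taken during labour. Keeping a woman who has delivered in the trial does not create a 45-minute score for her, nor a before-and-after difference. The time point is also later than the 30-minute one at which the previous trial lost women, and the article criticises earlier trials for the same kind of loss.

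A t-test or Mann–Whitney test uses only the scores that exist. At 45 minutes it therefore compares women who are still undelivered, a group defined after randomisation, although the section says all randomised women are analysed. At stake is how far the 45-minute result can be read as a comparison of the randomised groups.

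**Working it through.** **The plan's own figures.** The article gives no figure for women who deliver before 45 minutes. Its sample size supplies the denominator. For 17.5% against 12.5%, two-sided 0.05 and 80% power, the two-proportion formula gives 800 per group without continuity correction and 839 with it, as stated. Allowing for 10% attrition, 839 / 0.90 = 932.2, so 933 per group and 1866 in total. That is the Abstract's total. Sample size says 1886, a separate matter that changes the counts below by at most four women.

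**Inputs for the loss.**

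- From Sample size: 13% attrition in the previous trial, with a 30-minute pain score.
- From Secondary outcomes: scores at 10 and 45 minutes.
- Assumed: the share *s* of the 13% that was birth before 30 minutes (the article names two causes without a split), a constant rate of birth, and a population like the previous trial's.

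**Formulas.** Births by 30 minutes: p = 0.13 × s. By 45 minutes: 1 − (1 − p)^(45/30). By 10 minutes: 1 − (1 − p)^(10/30).

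| Assumed share s | p at 30 min | Lost at 45 min | Women of 1866 | Lost at 10 min |
|---|---|---|---|---|
| 25% | 3.25% | 4.8% | 90 | 1.1% |
| 50% | 6.5% | 9.6% | 179 | 2.2% |
| 75% | 9.75% | 14.3% | 266 | 3.4% |
| 100% | 13% | 18.9% | 352 | 4.5% |

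A straight-line extrapolation, 1.5 × p, gives nearly the same: 9.75% at a half share and 19.5% at a full share.

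**Could this bias the comparison?** Suppose women who deliver early would have scored 2 cm higher than the others. The observed difference between arms then shifts by (difference in early-birth proportion) × 2 cm. If the arms differed by 5 to 9 percentage points, the shift would be 0.05 × 2 = 0.10 cm to 0.09 × 2 = 0.18 cm. With an assumed SD of 2.5 cm and 14% missing, the standard error is 2.5 × √(2 / (933 × 0.86)) = 0.125 cm, so the shift is 0.8 to 1.4 standard errors. The 2 cm, the SD and the 5 to 9 points are all assumptions. With equal early-birth proportions the shift is 0 × 2 = 0.

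**The case against.** The strongest reply is that the article shows neither the size of the loss nor any bias.

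- **Size.** A reader might infer that the plan itself implies a loss of 10% to 19%. It does not. The 13% covers all causes, and nitrous oxide is named alongside early birth. The lower end assumes a half share and the upper end a full share. The consent limit also screens out some women close to birth. All of this stands.
- **Reach.** A reader might infer that the whole analgesic result rests on a selected subset. It does not, because the 10-minute score is little affected.
- **Bias.** A reader might infer that the 45-minute result is biased because the injections change the speed of labour. The stated hypothesis concerns caesarean section; length of labour is only a listed outcome. A 9-point difference around 14% means roughly 10% against 19%, nearly a doubling, and nothing in the article supports it. Even then the shift is 1 to 2 mm on a 100 mm scale.
- **Missing rule.** How absent scores are handled may be set out in a full protocol or analysis plan that is not shown, or in the cited Cochrane format. The lack of a rule in the article is therefore not itself an error.
- **Attrition statement.** It stands in a section that sizes the trial for caesarean section. That is fair, but the statement is general and its evidence comes from a trial with a pain outcome, so it should say which outcome it covers.

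What remains is that a labour pain score cannot be taken after birth, and that the named two-sample tests use only observed scores.

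**Conclusion.** The point holds in a limited form. The 45-minute score is undefined for women who have delivered, and the stated two-sample comparison at 45 minutes describes women still in labour rather than all women randomised. The likely loss runs from a few percent to about 19%. That range rests on an unstated split of the 13% and a constant birth rate, and the consent limit lowers it by an unknown amount. At 10 minutes the loss is about 1% to 4.5% for shares of a quarter to all.

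The change in the population described is firm. Bias between arms is only possible, and is near zero if early-birth rates are equal. The outcome is secondary and unpowered, so the point is minor.

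**What to change.** 1. In Statistical methods, replace the unadjusted two-sample tests for VAS with one model of the 10- and 45-minute scores, adjusted for baseline VAS and site (the randomisation stratum). Give the treatment contrast at each time. A woman who delivers before 45 minutes still contributes her 10-minute score. Read the 10-minute contrast as the one least affected by early birth.
2. Report by arm the number delivered before 45 minutes.
3. State that the observed 45-minute comparison applies to women still in labour. Present the model-based 45-minute estimate as supportive, because it implicitly projects scores past birth and so answers a different question.
4. In Sample size, limit the expectation of little attrition to the primary outcome.

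The cost is some wording, one count per arm and slightly more analysis. Baseline VAS, site and time of birth are already part of the trial's data. The downside is a narrower statement about pain at 45 minutes.
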